### **6.3 Primary Endpoint**

1. Number and proportion of patients with clinical response at the end of observational treatment period that is determined based on the Scale for Vestibular Vertigo Severity Level and Clinical Response Evaluation (SVVSLCRE) (Figure 1 and Table 1) in the total program population.

The patients will evaluate vestibular vertigo severity at baseline and end of observational treatment period based on the SVVSLCRE.

[figure not shown]

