#### **6.4 Secondary Endpoints**

1. Number and proportion of patients in each category of SVVSLCRE at baseline and end of observational treatment period in patients who completed betahistine treatment over a period less or equal 30 days and in patients who completed betahistine treatment over a period more than 30 days but less or equal 60 days.
2. Change of the patient's clinical conditions of vestibular vertigo assessed with SVVSLCRE from baseline to the end of observational treatment period in patients who completed betahistine treatment over a period less or equal 30 days and in patients who completed betahistine treatment over a period more than 30 days but less or equal 60 days.
3. Change of the patient's clinical conditions of vestibular vertigo assessed with SVVSLCRE from baseline to Visit 2 in patients who completed betahistine treatment over a period more than 30 days but less or equal 60 days.

[figure not shown]

4. Change of vestibular vertigo attacks frequency from baseline to the end of observational treatment period in patients who completed betahistine treatment over a period less or equal 30 days and in patients who completed betahistine treatment over a period more than 30 days but less or equal 60 days.
5. Change of vestibular vertigo attacks frequency from baseline to Visit 2 in patients who completed betahistine treatment over a period more than 30 days but less or equal 60 days.
6. Overall clinical response assessed by physician will be determined based on a four-point-scale, where 4 = excellent, 3 = good, 2 = fair, and 1 = poor. Proportion of patients in each category at the end of observational treatment period will be determined in patients who completed betahistine treatment over a period less or equal 30 days and in patients who completed betahistine treatment over a period more than 30 days but less or equal 60 days. Proportion of patients in each category at Visit 2 will be determined in patients who completed betahistine treatment over a period more than 30 days but less or equal 60 days.

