## **7.4 Program Duration**

Each patient will be observed approximately 2 months within the observational treatment period and approximately 2 months within follow-up period for the evaluation during the course of vestibular vertigo after Betaserc® treatment discontinuation. Based on underlying ICD-10 diagnosis and the clinical judgment of the physician, duration of treatment period

[figure not shown]

can be less than 2 months or can continue after termination of program's observational treatment period. However, only patients who finish betahistine dihydrochloride (Betaserc®) within 1 - 2 months of therapeutic period will be observed for the assessment of the course of vestibular vertigo within 2 months of follow-up period.

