| Overall clinical response and clinical response as improvement of vestibular vertigo associated symptoms based on four-point scales  |                        | X                                                                                 | X                                                                                 |                                                                    |                                                           |
| SAE monitoring                                                                                                                       | X                      | X                                                                                 | X                                                                                 | X                                                                  |                                                           |

 This program does not include patients who required betahistine therapy, according to physician's decision, more than 60 days.

 Actual date of visit may be up to 7 days from the last betahistine dose, otherwise proceed to Visit 4.

[figure not shown]

 This coincides with Visit 2 in case patient had completed betahistine treatment period lasting 30 days or less. In case physician decides to continue betahistine therapy beyond 30 days, Visit 3 will be a separate visit from Visit 2.

 For patients whom physician decides to continue betahistine therapy beyond 60 days treatment course, no follow up will be done and end of observational treatment period will denote end of program.

 Includes sex, age, race (white, black, asian, other), weight and height

 Heart rate, blood pressure (systolic and diastolic)

 for more detailed information about Scale for Vestibular Vertigo Severity Level and Clinical Response Evaluation please see section 6.3, Figure 1 and Table 1.

 Four-point-scale, where 4 = excellent, 3 = good, 2 = fair, and 1 = poor.

 30 days after end of program treatment or early termination, a telephone call will be made to enquire about development of any SAE. If there is a positive feedback, relevant medical history and adverse event details will be collected.

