### Data Analysis Set

**All Patients Set** will include all patients who signed patient authorization form to participate in the study. This population will be used for presenting disposition of subjects.

**Full Analysis Set** will include those patients who attended Visit 1 and who were administered at least one dose of betahistine dihydrochloride (Betaserc®), as assessed in the CRF. This population will be used for the reporting of effectiveness results.

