### **Secondary Endpoints**

Analysis of secondary endpoints will be done only for supporting evidence without any intention for a claim of treatment benefit for the secondary endpoints. Therefore, p-values and confidence intervals for secondary endpoints are purely for descriptive purposes and not for drawing inferences.

1. Number and proportion of patients in each category of SVVSLCRE at baseline and the end of observational treatment period will be presented for patients who completed betahistine treatment over a period less or equal 30 days and for patients who completed betahistine treatment over a period more than 30 days but less or equal 60 days.
2. Change of the patient's clinical conditions of vestibular vertigo assessed with SVVSLCRE from baseline to the end of observational treatment period will be presented with median, 1st quartile and 3rd quartile. Comparison between baseline and the end of observational treatment period will be made using Wilcoxon signed-rank test for dependent variables. Test statistic and p-value will be presented for each comparison. Tests resulting in p-values less than or equal to 0.05 will be reported as "statistically significant".
3. Change of the patient's clinical conditions of vestibular vertigo assessed with SVVSLCRE from baseline to Visit 2 will be presented with median, 1st quartile and 3rd quartile. Comparison between baseline and Visit 2 will be made using Wilcoxon signed-rank test for dependent variables. Test statistic and p-value will be presented for each comparison. Tests resulting in p-values less than or equal to 0.05 will be reported as "statistically significant".

[figure not shown]

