### **Sample size considerations**

Based on evaluation of literature data that was published by Gananca et al. in *Acta Oto-Laryngologica*, 2009 [17], proportion of patients with Meniere's Disease achieved control of vertigo (clinical conditions levels 4 and 3) after 12 weeks of treatment with betahistine dihydrochloride tablets constituted 88%. Benecke et al. [18] found that overall efficacy of betahistine in routine clinical practice over 3 months therapy was excellent by 36.6% of 1753 patients with recorded data (n = 641) and good by 49.6% of patients (n = 870), total 86.2 %. The investigators' impression of the treatment was excellent for 38.6% of patients (n = 675 of 1747) and good for 50.5% of patients (n = 883), total 89.1%.

For this program, it is assumed that at least 80% of the total study sample will achieve clinical response after 60 days of therapy with betahistine dihydrochloride tablets. When the sample size without a consideration of dropout is 246, a normal approximation two-sided 95% confidence interval for a single proportion using normal distribution will extend 5.0% (i.e. half width of the 95% confidence interval) from the observed proportion for an expected proportion of 80% [19; 20]. Considering an approximate dropout rate about 20%, total study population (received at least one dose of betahistine dihydrochloride (Betaseron®) tablets and have at least one post-baseline assessment) will constitute 308 patients.

Overall, the best consideration for total number of enrolled patients with vestibular vertigo in the program has to amount 310.

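### Visit 2 results in section 6.4 are limited to patients who later completed 31–60 days of treatment, a group defined after Visit 2, and section 11 does not carry the same restriction

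*Protocol*

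**What the plan says.** Section 6.4 items 3 and 5 of the Protocol define the Visit 2 changes in severity level and attack frequency "from baseline to Visit 2 in patients who completed betahistine treatment over a period more than 30 days but less or equal 60 days". Items 6–9 place the same limit on the Visit 2 part of the four-point ratings.

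The footnotes to Table 2 (section 7.5) cover the other patients. On the end-of-treatment visit, footnote 3 says: "This coincides with Visit 2 in case patient had completed betahistine treatment period lasting 30 days or less". Footnote 4 provides for a further group: "For patients whom physician decides to continue betahistine therapy beyond 60 days treatment course, no follow up will be done".

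Section 7.4 says what sets the length of treatment: "Based on underlying ICD-10 diagnosis and the clinical judgment of the physician, duration of treatment period" may be shorter than two months or may run on past the observed period.

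In section 11, item 3 says only that the change "from baseline to Visit 2 will be presented with median, 1st quartile and 3rd quartile", with no duration group named. Item 5 (attack frequency) names none either, whereas section 11 items 6–9 keep the limit. The general rule for the Full Analysis Set is "This population will be used for the reporting of effectiveness results".

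The primary endpoint (section 6.3) is assessed at the end of observational treatment "in the total program population". The sample size text assumes that "at least 80% of the total study sample will achieve clinical response after 60 days of therapy".

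**The concern.** A patient belongs to the 31–60-day group because of what happened after Visit 2. Summarising a measurement taken by day 30 only in patients who then went on to a particular treatment course conditions on the future. If the physician's decision to stop or continue reflects how the patient is doing, patients who did well early, and those who did badly enough to continue past 60 days or to leave, drop out of the Visit 2 summary. What remains does not describe early response among everyone treated.

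Two further points follow. An analyst working from section 6.4 and one working from section 11 with the Full Analysis Set rule would produce different Visit 2 tables. And the planning text describes response at a single time, day 60, whereas the endpoint is rated whenever observed treatment ends.

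**Working it through.** **1. The plan's own figure.** Inputs from the sample size text: expected proportion 0.80, half-width 0.05, two-sided 95% interval, normal approximation, dropout 20%.

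- n = 1.96² × 0.80 × 0.20 / 0.05² = 245.85, rounded up to 246. Reproduced.
- 246 / 0.80 = 307.5, rounded up to 308. Reproduced; enrolment is 310.

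Nothing in this point disturbs these numbers.

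**2. Where each patient's Visit 2 data go under section 6.4.**

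| Treatment course | Visit 2 result reported? |
|---|---|
| Completed in 30 days or less | Only as the end-of-treatment result, which is the same visit |
| Completed in 31–60 days | Yes (items 3, 5 and 6–9) |
| Continued beyond 60 days | Under no effectiveness endpoint in 6.4 |
| Terminated early | Under no effectiveness endpoint in 6.4 |

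Table 2 schedules the severity scale, attack count and four-point ratings at Visit 2 without any duration condition, so the data are planned for collection.

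**3. Can the tables be recombined?** For the four-point ratings (counts by category), adding the two duration groups largely rebuilds a Visit 2 distribution, apart from the last two rows above. For severity change it does not: section 11 gives medians and quartiles, and the medians of two groups do not determine the median of both together.

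**4. Section 6.4 against section 11.** Items 3 and 5 carry the limit in 6.4 and not in 11; items 6–9 carry it in both. Section 11 item 5 also compares baseline with Visit 2 but asks for descriptive statistics at baseline and at end of treatment.

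**5. Possible size (all inputs assumed).** The Protocol gives no stopping shares and no response rates by duration. Take a Visit 2 response proportion, such as Table 1 categories applied at Visit 2 would give. Let f be the share stopping by day 30, r1 their response and r2 the response of the rest. The all-patient value is f × r1 + (1 − f) × r2, so the restricted figure falls short by f × (r1 − r2).

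- f = 0.10, r1 = 95%, r2 = 70%: 0.10 × 25 = 2.5 points.
- f = 0.30, r1 = 90%, r2 = 60%: 0.30 × 30 = 9.0 points.
- f = 0.50, r1 = 95%, r2 = 60%: 0.50 × 35 = 17.5 points.
- r1 = r2: 0 points at any f.

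Patients continuing beyond 60 days could pull the other way. With assumed responses of 90%, 60% and 30% in the three duration groups:

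- A 30/60/10 split gives 27 + 36 + 3 = 66%, against 60% in the middle group.
- A 10/50/40 split gives 9 + 30 + 12 = 51%, against the same 60%.

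The direction is therefore not fixed. The second split is extreme, because section 7.1 says the program does not include patients judged to need more than two months.

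**6. Precision.** At 80% response the half-width is 1.96 × √(0.16/n), or 5.0 points with all 246. If 10%, 20%, 30% or 50% stop by day 30 (assumed), the remaining 221, 197, 172 or 123 give 5.3, 5.6, 6.0 or 7.1 points.

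**7. The planning phrase.** Suppose every patient responding at day 30 stops there and the rest are rated at day 60. Let response be q at each time, with within-patient correlation φ. End-of-treatment response then exceeds day-60 response by (1 − φ) × q × (1 − q).

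- For q from 0.80 to 0.60: 16 to 24 points at φ = 0, and 8 to 12 points at φ = 0.5.
- At φ = 1: 0 points.

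This is an illustration of why the two descriptions are not interchangeable, not an estimate for this program.

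**The case against.** The layout has a sensible purpose. Only the 31–60-day group has a Visit 2 separate from the end visit, so a Visit 2 row for that group shows a within-patient course and avoids reporting the same visit twice. Patients treated for 30 days or less are not lost; their rating appears as the end-of-treatment result. This stands, and it reduces the gap to patients who continue or terminate early, plus the lack of any combined summary.

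The result is labelled as a subgroup result, and secondary analyses are declared descriptive. That limits the harm, but a descriptive figure still needs one stated population. Section 11 might be read as shorthand for 6.4, since its items 2 and 4 omit the duration groups too. That is possible, but the general Full Analysis Set rule points the other way, so the text needs settling.

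Items 3 and 5 report changes in severity and attack counts, not a response percentage, so the percentages in the working have no planned counterpart there. This also stands; they are illustrations only.

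A reader might infer that no response estimate in the plan is free of selection on the outcome. The documents do not support that: the primary endpoint covers the total program population and excludes no one by duration. A reader might also infer that treatment ends because the patient has recovered. Section 7.4 names diagnosis and clinical judgment, not recovery; a link with response is plausible but not stated. Nor is Visit 2 available for everyone: Table 2 footnote 2 sends patients seen more than 7 days after the last dose on to Visit 4, where the severity scale is not scheduled.

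**Conclusion.** The point holds as a cheap improvement. The Visit 2 summaries in 6.4 are selected on later treatment course; patients continuing beyond 60 days or terminating early are reported at Visit 2 nowhere among the effectiveness endpoints; and 6.4 and section 11 disagree on the population for items 3 and 5. These follow from the text alone.

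Whether the selection distorts the picture rests on an assumption the Protocol neither makes nor rules out: that treatment duration is related to response. Without that relation the distortion is zero. With it, the size cannot be known from the documents.

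The primary analysis is not invalidated. Its assessment time varies with the physician-set end of treatment, so the sample size text describes it wrongly, but 246, 308 and 310 stand.

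**What to change.** - In section 6.4 and section 11, report Visit 2 severity change, attack frequency, four-point ratings and the Table 1 shift categories applied to Visit 2 for all Full Analysis Set patients with a Visit 2 assessment, including those who continue beyond 60 days or terminate early.
- Keep the duration groups as a breakdown, labelled as defined after baseline.
- Name the same population in both sections for items 3 and 5.
- State that for patients treated for 30 days or less the Visit 2 rating is also the end-of-treatment rating. The all-patient summary is then near-common in time; it is not a fixed-time check on the primary endpoint.
- In the sample size text, replace the reference to 60 days of therapy with response at the end of observational treatment (up to 60 days).

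The cost is wording in two sections, one more table column and some repeated reporting for the group treated for 30 days or less. No new data are needed and the sample size does not change.

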## 7.0 Investigational Plan

The program is designed as a prospective, multicentre, observational, non-interventional, non-randomized, non-controlled, single arm, Post-Marketing program.

### 7.1 Selection of Study Population

This is a prospective, multinational, non-comparative, Post-Marketing observational program in patients whom betahistine dihydrochloride (Betaserc®) tablets were prescribed in the usual manner at the maximal recommended daily dose of 48 mg in accordance with the locally approved label (prescribing information/summary of product characteristics). Over a program period physician is free to adjust Betaserc® dose according to country approved label.

Adult patients who can be treated with betahistine dihydrochloride as per the locally approved label (vestibular vertigo) will be enrolled in the study. This program does not include patients who required betahistine therapy, according to physician's decision, more than 2 consecutive months.

The dosage 48 mg will be under investigation and can be divided over the day as following:

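### The protocol both leaves out and keeps patients treated beyond 60 days, and Sections 6.4 and 11.0 disagree on whether the treatment-period secondary endpoints cover them

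*Protocol*

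**What the plan says.** **Who is in the program.** Section 7.1 says: "This program does not include patients who required betahistine therapy, according to physician's decision, more than 2 consecutive months". Table 2 footnote 1 says the same in days: "This program does not include patients who required betahistine therapy, according to physician's decision, more than 60 days". Section 7.4, however, lets the physician set the duration from the diagnosis and clinical judgment, and says it "can be less than 2 months or can continue after termination of program's observational treatment period". Table 2 footnote 4 gives the handling: "For patients whom physician decides to continue betahistine therapy beyond 60 days treatment course, no follow up will be done", and for these patients the program ends when the observational treatment period ends. Neither eligibility list (7.1.1, 7.1.2) has a criterion on treatment duration.

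**Who is analysed.** Section 6.3 defines the primary endpoint in the total program population. The FAS in Section 11.0 requires attendance at Visit 1 and one dose, and is the set for effectiveness results. Section 6.4 reports endpoints 1-11 "in patients who completed betahistine treatment over a period less or equal 30 days" and/or in those who completed in more than 30 and up to 60 days. Endpoint 12 uses all patients. Section 11.0 repeats the duration groups in items 1 and 6-10 but not in items 2-5.

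**How tests are reported.** Section 11.0 calls secondary p-values and confidence intervals "purely for descriptive purposes and not for drawing inferences". For each tested item it then adds: "Tests resulting in p-values less than or equal to 0.05 will be reported as" statistically significant.

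**The concern.** The FAS keeps a patient who is still on treatment after day 60, and Table 2 footnote 4 keeps that patient to the end of the observational treatment period. The literal wording of Section 7.1 and footnote 1 puts the same patient outside the program, and so outside the total program population on which the primary endpoint is defined. A programmer could defend either denominator, and the choice could be made after outcomes are known.

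The secondary endpoints have a related problem. Whether a patient completes within 60 days is settled by a physician's decision after baseline, and that decision may be related to how the patient is doing. Section 6.4 makes it a condition for entering endpoints 1-9. Patients who continue have severity-scale scores, attack counts and four-point ratings at Visits 2 and 3, yet no group in 6.4 reports them. For endpoints 2-5, Section 11.0 does not apply the condition, so the two sections specify different populations for tested endpoints. The significance label then gives these results more weight than the section's own disclaimer allows.

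**Working it through.** **1. The plan's own figure.** Inputs from the sample size section: expected response 0.80, two-sided 95% interval, half-width 0.05, dropout 20%.

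- n = 1.96² × 0.80 × 0.20 / 0.05² = 245.9, rounded up to 246.
- 246 / (1 − 0.20) = 307.5, rounded up to 308; 310 are to be enrolled.

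Both figures reproduce. Nothing here changes N.

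**2. Where a patient treated beyond day 60 falls.**

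| Text | Status of that patient |
|---|---|
| 7.1; Table 2 footnote 1 | not in the program |
| 7.4; Table 2 footnote 4 | in, to the end of the observational treatment period; no follow-up |
| 6.3, primary endpoint | depends on which of the above defines the program population |
| 11.0, FAS | in |
| 6.4, endpoints 1-9 | in no reported group |
| 11.0, items 1 and 6-9 | in no reported group |
| 11.0, items 2-5 | no duration limit stated |
| 6.4 endpoints 10-11; 11.0 item 10 | out, necessarily: no post-treatment period observed |

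**3. Tests carrying the label.** Under 6.4, endpoints 2, 4, 10 and 11 are each tested in two duration groups and endpoints 3 and 5 in one: 4 × 2 + 2 × 1 = 10. Of these, 2 × 2 + 2 × 1 = 6 concern the treatment period. Under 11.0 as worded, items 2-5 give 4 tests without a duration limit, and item 10 gives two time points in two groups, so 4 + 4 = 8. The two sections do not even yield the same number of tests.

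**4. Illustration for the primary proportion, if the literal reading of 7.1 removed continuing patients.** Let f be the share continuing and r their response rate. Neither is in the protocol; both are assumed. With 80% responding overall, the rate in the remaining patients is (0.80 − f × r) / (1 − f). For example, f = 0.10 and r = 0.40 give (0.80 − 0.04) / 0.90 = 84.4%.

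| f | r = 90% | r = 80% | r = 60% | r = 40% | r = 20% |
|---|---|---|---|---|---|
| 5% | 79.5% | 80.0% | 81.1% | 82.1% | 83.2% |
| 10% | 78.9% | 80.0% | 82.2% | 84.4% | 86.7% |
| 20% | 77.5% | 80.0% | 85.0% | 90.0% | 95.0% |

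The shift is zero if continuing patients respond like the rest, and it reverses if they respond better. The planned 5-point half-width is a fair yardstick for this proportion only. It says nothing about endpoint 2, which is a median change.

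**5. Illustration for a labelled test.** 246 normally distributed changes with true median zero were simulated. The share f with the lowest values of a score correlated rho with the change was removed, and the rest were tested with the Wilcoxon signed-rank test at 0.05 (1000 runs per setting). The chance of a labelled improvement was about 2.5% with nobody removed. With 10% removed it was 14%, 45% and 77% for rho = 0.3, 0.6 and 1.0. This assumes that the patients removed tend to be those doing worse, and it uses one pooled group rather than the two groups of 6.4. It shows what such selection could do, not what will happen here.

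**The case against.** The strongest defence is that the texts can be reconciled. Section 7.1 concerns selection of patients, so its sentence may mean that the physician does not expect treatment beyond two months at entry, with footnote 4 covering later changes of mind. That is possible, but the protocol does not say it. The eligibility lists are silent, footnote 1 hangs on the treatment-period column heading rather than the eligibility row, and footnotes 3 and 4 speak of decisions to continue beyond day 30 or day 60.

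The FAS definition is also a real protection: it has no duration limit and is named for effectiveness results. Followed as written, it leaves the primary analysis intact. And if Section 11.0 governs, tested items 2-5 can include continuing patients, so their omission follows from 6.4 rather than from the whole plan.

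A reader might infer that slow responders and non-responders are removed and the results are therefore biased towards benefit. The documents do not support that as a fact. Section 7.4 ties duration to diagnosis and clinical judgment, not to response. Section 5.0 describes courses of 2-3 months as aiding compensation, so a patient may continue while doing well, and a non-responder may stop early. A bias towards benefit is plausible but undocumented.

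A reader might also count the post-treatment endpoints 10 and 11 as affected. They are not: a patient still on treatment has no course after discontinuation to measure.

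Last, Section 11.0 disclaims any treatment-benefit claim from secondary endpoints. This limits the harm of the label, but does not remove the contradiction.

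**Conclusion.** The point holds as an inconsistency that should be fixed, not as a demonstrated bias. Three things stand on the text alone:

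- the passages conflict on whether patients treated past 60 days belong to the program, which leaves the primary denominator open on a literal reading;
- Section 6.4 conditions the treatment-period endpoints 1-9 on a post-baseline decision and leaves continuing patients' Visit 2 and 3 data unreported, while Section 11.0 items 2-5 state no such condition;
- the significance label conflicts with the descriptive purpose declared in the same section.

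Neither the size nor the direction of any effect can be established from the protocol. The figures above rest on assumed shares and response rates and include no shift at all. It would be too strong to say that the primary result is biased, since the FAS as defined keeps these patients. The sample size is unaffected.

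**What to change.** 1. Reconcile Section 7.1 and Table 2 footnote 1 with Section 7.4 and Table 2 footnote 4, so that one statement says who belongs to the program and whether the duration sentence applies at entry or later.
2. State that no patient leaves the FAS or the primary analysis because treatment continued past day 60.
3. Report endpoints 1-9 at the end of the observational treatment period for the whole FAS and by three descriptive duration groups: up to 30 days, 31-60 days, and continuing beyond 60 days. Give Visit 2 results for all patients with a Visit 2 assessment.
4. Word Section 11.0 items 2-5 and Section 6.4 so that they name the same populations.
5. Leave endpoints 10 and 11 restricted to patients who stopped treatment.
6. Delete the significance sentences from the secondary analyses and give the median or mean change with a 95% confidence interval, in line with the section's own disclaimer.

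The cost is wording and extra table columns. The Visit 2 and 3 data are already scheduled for collection. Secondary results may look less favourable once continuing patients are shown.
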